### Concealment mechanism {16b}

Upon enrollment in the study, each participant is assigned an internal identifying number (ID) that is used for the allocation sequence. A blinded researcher implements the allocation after the baseline evaluation conclusion by accessing the randomization list based on the participants’ ID. Participants are allocated into one of the three groups and informed about their intervention (water-based exercise intervention group, land-based exercise intervention group, or health education active control group) via telephone or message.

### Implementation {16c}

[name] is the researcher responsible for generating the allocation sequence, [name] is the researcher responsible for enrolling participants, and [name] is the researcher responsible for assigning participants to interventions.

## Assignment of interventions: blinding

### Who will be blinded {17a}

Blinding is implemented for outcome assessors and data analysts responsible for evaluating both primary and secondary outcomes. However, due to the inherent nature of the interventions, neither the staff conducting the exercise or health education sessions, nor the participants are blinded. Participants are instructed to refrain from disclosing their assigned group and discussing their interventions during outcomes assessments to ensure the assessor masking.

### Procedure for unblinding if needed {17b}

In the case of unintentional unblinding for any reason, researchers involved are required to notify the coordinator. This information is then documented for internal control purposes.

## Data collection and management

### Plans for assessment and collection of outcomes {18a}

On the initial visit, after signing the consent form, each participant completes a questionnaire covering their clinical and sociodemographic characteristics. During this visit, familiarization procedures are also performed with the knee extension equipment, treadmill, and RPE scale to mitigate potential learning biases and ensure participants’ proficiency in performing the tests before formal data collection.

The study outcomes are assessed at two time points: baseline (weeks 0) and post-intervention (week 13). All randomized participants undergo outcome assessments, irrespective of their attendance or completion status. Participants who withdraw from the study at any time after randomization are still invited to complete the final evaluations (week 13), ensuring data inclusion in the intention-to-treat analysis. Measurements are performed in two separate visits, apart at 48-h interval to avoid interference among them, according to the sequence:Visit 1: quality of life questionnaire, cancer-related fatigue questionnaire, perceived cognitive function questionnaire, mental health questionnaire, maximal dynamical strength of knee extensors, dynamic muscular endurance of knee extensors, and functional testsVisit 2: quality and thickness of quadriceps, objective cognitive function instruments, pain questionnaire, physical activity levels questionnaire, anthropometric measurements, office blood pressure, cardiorespiratory fitness test and food frequency questionnaire

Participants are instructed to avoid intense physical activity 72 h before the first evaluation session (week 0). Post-intervention evaluations take place 72 h after the last training session. In addition, the follow-up questionnaire is applied on the last visit of the final evaluations.

The same investigator applies each test at baseline and post-intervention time points to ensure consistency. Outcome assessors are trained, and standardized procedures are performed for each assessor during assessments. In addition, the same investigator applies the questionnaires individually at baseline and post-intervention time points in a reserved room.

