**Discussion:**

Our conceptual hypothesis is that both aerobic exercise programs will positively impact primary and secondary outcomes compared to the health education group alone. Additionally, due to its multi-component nature, we expect the aquatic exercise program promote more significant effects than the land exercise program on cancer-related fatigue, muscular outcomes, and pain.

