##### Muscular performance

The maximum dynamic muscle strength of knee extensors is measured the one-repetition maximum (1RM) test in a knee extension equipment (Sportmania Fitness, Novo Hamburgo, RS, Brazil). The 1RM value is considered the greatest load that the participant could lift for one complete repetition (i.e., concentric and eccentric phase) following a predetermined cadence (i.e., approximately 2 s per phase) controlled by a digital app (Metronome). The 1RM of each participant is determined within five attempts, and at least 3 min of rest interval was given between trials. A new load was estimated following Lombardi’s coefficient [44] for the subsequent trial when the participant could perform more than one complete repetition. The test is rescheduled if the value of 1RM is not determined between the five attempts. According to a previous study from our laboratory [35], the range of motion is being individualized for each participant and controlled by a range of motion custom-build device.

The same knee extension equipment is used to assess dynamic muscular endurance. Participants perform the maximal number of bilateral knee extension repetitions with 60% of individual 1RM load. The test cadence (2 s for each contraction phase) and range of motion are the same for the 1RM test. The post-intervention assessment is performed using the same absolute load employed at baseline (i.e., 60% of baseline 1RM).

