##### Pain

Pain is measured using the BPI, which has been validated for Brazilian cancer patients [52]. This instrument consists of nine multidimensional items that assess pain intensity, pain interference in the patient’s life, pain location, and treatments for pain control and relief. Responses are given on a scale from 0 to 10, reflecting the pain felt at the time of the questionnaire and in the past 24 h. Scores are calculated by averaging the total items. A higher score indicates greater pain severity.

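### Pain and quadriceps ultrasound are taken 48 h after maximal knee-extensor testing, a shorter gap than the 72 h the protocol uses elsewhere, so test after-effects may carry over into these secondary outcomes

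*Protocol article*

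**What the plan says.** All references are to the protocol article.

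- **Order and gap.** Plans for assessment and collection of outcomes {18a} states: "Measurements are performed in two separate visits, apart at 48-h interval to avoid interference among them". Visit 1 lists four questionnaires (quality of life, fatigue, perceived cognition, mental health), then knee-extensor strength, knee-extensor endurance and the functional tests. Visit 2 opens with "quality and thickness of quadriceps, objective cognitive function instruments, pain questionnaire, physical activity levels questionnaire". Table 3 assigns pain and muscle morphology to the second visit at both time points, in agreement with the text.
- **Load at visit 1.** Under Muscular performance: "The 1RM of each participant is determined within five attempts, and at least 3 min of rest interval was given between trials". Each repetition has a concentric and an eccentric phase. For endurance: "Participants perform the maximal number of bilateral knee extension repetitions with 60% of individual 1RM load". At week 13 the endurance load is the same absolute load as at baseline.
- **Pain recall.** Under Pain, responses are described as "reflecting the pain felt at the time of the questionnaire and in the past 24 h".
- **Rest intervals elsewhere in {18a}.** "Participants are instructed to avoid intense physical activity 72 h before the first evaluation session (week 0"), and "Post-intervention evaluations take place 72 h after the last training session".
- **Length of the assessment period.** A footnote to Table 3 allows up to 2 weeks for the baseline and final assessment periods.
- **Role of these outcomes.** Pain and muscle morphology are secondary. The abstract's Discussion expects the aquatic programme to "promote more significant effects than the land exercise program on cancer-related fatigue, muscular outcomes, and pain".

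**The concern.** The protocol gives avoidance of interference as the reason for the 48-h gap. Yet the muscle scanned at visit 2 is the one worked to its maximum at visit 1, and the pain questionnaire looks back over a period that falls entirely after that work. Where the protocol guards against other exercise affecting its measurements, it asks for 72 h. It gives no reason for accepting 48 h after its own maximal tests.

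The other symptom questionnaires come before the strength tests. Pain, the symptom most open to an effect of muscle loading, comes after them.

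If an after-effect remains at 48 h, the change in pain, thickness and echo intensity contains a reaction to testing as well as any effect of the intervention. With 48 women in three arms (16 per arm), extra noise is unwelcome. A reaction that differed between trained and untrained women would also bias the exercise-control comparisons.

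**Working it through.** The plan gives no figure to reproduce here. The check is a time line, followed by the arithmetic of what an after-effect would do.

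**1. Time line, with the visit-1 strength tests at hour 0**

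| Event | Hours after the tests |
|---|---|
| Start of the 24-h pain recall | 48 − 24 = 24 |
| Pain questionnaire and ultrasound (visit 2) | 48 |
| Interval the protocol uses elsewhere | 72 |
| Shortfall | 72 − 48 = 24 |

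The whole recall window (24 to 48 h) falls inside 72 h. Training itself is not the source: at week 13, visit 2 comes at least 72 + 48 = 120 h after the last session. The treadmill test is not the source either, because it is listed after pain and ultrasound within visit 2.

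**2. Bias in the between-arm difference in change**

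Let b be the shift that the tests add at baseline and p the shift at week 13, in SD units, for exercise (E) and control (C).

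Bias = (p_E − b_E) − (p_C − b_C)

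Before any intervention b_E = b_C is expected, so the bias reduces to p_E − p_C. The documents give no shifts. The values below are assumptions, with b = 0.3 in both arms and p_C = 0.3.

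| p_E | Calculation | Bias (SD) |
|---|---|---|
| 0.4 | (0.4 − 0.3) − (0.3 − 0.3) | +0.1 |
| 0.3 | (0.3 − 0.3) − (0.3 − 0.3) | 0 |
| 0.2 | (0.2 − 0.3) − (0.3 − 0.3) | −0.1 |
| 0.1 | (0.1 − 0.3) − (0.3 − 0.3) | −0.2 |
| 0 | (0 − 0.3) − (0.3 − 0.3) | −0.3 |

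If no after-effect remains at 48 h, every shift is 0 and so is the bias.

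**3. Which row applies?**

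The protocol points both ways.

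- *Smaller reaction in the exercise arms.* Regular exercisers are excluded at entry and other exercise is discouraged during the study. By week 13 the exercise arms have been offered 24 supervised sessions that the controls have not. A woman who has become stronger also meets the fixed endurance load at a lower share of her current maximum.
- *Equal or larger reaction.* The 1RM is a maximum, so a stronger woman lifts a heavier load. Endurance is scored as the greatest number of repetitions, so she also performs more of them.

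**4. Noise from an after-effect that is equal on average**

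Suppose the after-effect varies between women with SD s, as a fraction of the outcome SD and independently of the outcome. The standardized effect is then multiplied by 1/√(1 + s²).

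| s (assumed) | Factor |
|---|---|
| 0.2 | 1/√1.04 = 0.98 |
| 0.4 | 1/√1.16 = 0.93 |
| 0.6 | 1/√1.36 = 0.86 |

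**The case against.** The case for leaving the schedule alone has real weight.

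- **No stated rule is broken.** A reader might infer that the protocol violates its own washout. It does not: the 72-h intervals attach to activity before the first evaluation and to the last training session, and 48 h is the interval set between visits. A training session and a short series of maximal tests are also different exposures. What stands is an unexplained difference between two intervals that serve similar purposes.
- **Carry-over is not shown.** The documents hold no data on soreness, swelling or echo intensity at 48 h. Women are familiarised with the knee-extension equipment beforehand, and the 2-week footnote leaves open whether 48 h is exact or a minimum. This stands in full. The point is a risk, not a demonstrated effect.
- **Testing is the same in every arm.** The tests, their order and the investigator are the same at both time points, so a common after-effect cancels. This also stands, and it confines bias to a reaction that differs by arm.
- **The direction is open.** A reader might infer that the error favours exercise on pain and echo intensity, or hides real muscle growth. The documents do not support this, because stronger women do more work in the week-13 tests.
- **Water versus land.** A reader might infer that the hypothesised advantage of water is tested on biased measures. Both exercise arms train the legs, and nothing in the protocol indicates that their reactions would differ from each other.

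None of this supplies a reason for placing pain and ultrasound after the loading tests.

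**Conclusion.** The timing is established with high confidence: at both time points, pain and quadriceps ultrasound follow maximal knee-extensor testing by 48 h, which is 24 h less than the interval the protocol uses elsewhere. Carry-over into pain, muscle thickness and echo intensity is therefore possible.

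If it is equal across arms, the cost is noise: a factor of 0.98 to 0.86 on the standardized effect for assumed s of 0.2 to 0.6. If the week-13 reaction differs by arm, the bias equals that difference: 0 to 0.3 SD in size under the assumed shifts, with either sign possible. Confidence in differential bias is moderate to low.

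Only secondary outcomes are exposed. The fatigue questionnaire is listed before the strength tests at visit 1, so the primary comparison is untouched. This is an avoidable weakness worth correcting, not a threat to the trial's main conclusion.

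**What to change.** - **Women whose baseline is not yet done.** Give the Brief Pain Inventory with the other questionnaires at the start of visit 1, and do the quadriceps ultrasound at visit 1 before the strength tests. Use this order at baseline and at week 13.
- **Women already assessed at baseline.** Keep the present order at week 13, so that each woman's two measurements stay comparable. Report how many women in each arm had each order.
- **If the ultrasound cannot move.** Reconcile the 48-h gap with the 72-h interval, or justify the difference. A 72-h gap fits within the 2-week period in Table 3. State whether 48 h is exact or a minimum.
- **If all baselines are complete.** Recruitment was expected to end by August 2024, so this may be the case. Leave the order unchanged, report the actual interval between visits, and list possible carry-over as a limitation for pain and muscle morphology.

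The change amends {18a} and Table 3 and needs no new test, staff or visit. It makes visit 1 somewhat longer. Made mid-trial, it leaves two assessment orders, tied to recruitment period, among 48 women. Because allocation continues at 1:1:1 in blocks, the orders should be roughly balanced across arms, but the sample is too small to say much about order itself.

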#### Measurement of the primary outcome

##### Cancer-related fatigue

Cancer-related fatigue is measured using the PFS, a valid and reliable instrument for assessing fatigue in Brazilian cancer patients [41]. The PFS consists of 22 numerical items that assess the fatigue experienced by patients, using a 0–10 numeric scale. It measures four dimensions of subjective fatigue: behavioral/severity, affective meaning, sensory, and cognitive/mood. The total fatigue score is calculated by averaging the four subscale scores.

#### Measurements of secondary outcomes

##### Cardiorespiratory fitness

Cardiorespiratory fitness is determined by VO_2peak_ and ventilatory thresholds (i.e., VO_2VT1_ and VO_2VT2_) obtained by an incremental test on a treadmill (KIKOS, São Paulo—São Paulo, Brazil). First, the participants are kept seated at rest for 5 min in a calm environment to take HR measurements at rest using a heart rate monitor (H10, Polar, Kempele, Finland). Warming up is carried out for 3 min with a gradual increase in speed until reaching 3 km·h^−1^, and then the test starts at 3 km·h^−1^ with sequential increments of 0.5 km·h^−1^ every minute and a 1% increase in grade every 2 min until maximum effort. The test is finished when the participant can no longer exercise at a given workload, indicating exhaustion. All tests are supervised by a trained exercise physiologist and a physician.

Oxygen uptake is recorded during the incremental protocol using a mixing-box-type portable gas analyzer (VO2000, MedGraphics; Ann Arbor, USA) to determine participants’ VO_2peak_, VO_2VT1_, and VO_2VT2_. Data are acquired as an average of three breaths using the Aerograph software (MedGraphics; Ann Arbor, USA). Heart rate (HR) is obtained every 15 s using a heart rate monitor (FT1, Polar, Kempele, Finland), and participants’ RPE is assessed at the end of each stage with the Borg’s RPE 6–20 scale.

Tests are considered valid when at least two of the following criteria are met at the end of the test: maximal respiratory exchange rate ≥ 1.1, maximal estimated heart rate ≥ 220 bpm less age, and a maximal RPE ≥ 18 [42]. The individual VO_2peak_ is determined as the higher 15 s mean oxygen uptake value in the last test stage. The VT1 and VT2 are determined based on the ventilation by test stage plot and confirmed by the ventilatory equivalent of oxygen (VE/VO_2_) and carbon dioxide (VE/VCO_2_), respectively [43]. Two experienced physiologists independently detect thresholds by visual inspection while blinded to the participants’ experimental group. When there is no agreement among them, the opinion of a third physiologist is requested.

##### Muscular performance

The maximum dynamic muscle strength of knee extensors is measured the one-repetition maximum (1RM) test in a knee extension equipment (Sportmania Fitness, Novo Hamburgo, RS, Brazil). The 1RM value is considered the greatest load that the participant could lift for one complete repetition (i.e., concentric and eccentric phase) following a predetermined cadence (i.e., approximately 2 s per phase) controlled by a digital app (Metronome). The 1RM of each participant is determined within five attempts, and at least 3 min of rest interval was given between trials. A new load was estimated following Lombardi’s coefficient [44] for the subsequent trial when the participant could perform more than one complete repetition. The test is rescheduled if the value of 1RM is not determined between the five attempts. According to a previous study from our laboratory [35], the range of motion is being individualized for each participant and controlled by a range of motion custom-build device.

The same knee extension equipment is used to assess dynamic muscular endurance. Participants perform the maximal number of bilateral knee extension repetitions with 60% of individual 1RM load. The test cadence (2 s for each contraction phase) and range of motion are the same for the 1RM test. The post-intervention assessment is performed using the same absolute load employed at baseline (i.e., 60% of baseline 1RM).

##### Muscle morphology

Muscle thickness and muscle quality of the quadriceps femoris are measured from images obtained by B-mode ultrasonography (Toshiba—Tosbee/SSA-240A, Japan). Initially, the participants rest for 5 min in a supine position with legs extended and relaxed to stabilize the displacement of body fluids. Then, transversal images of the four portions of the quadriceps femoris are recorded with a 7.5-MHz linear array probe. Images of the vastus lateralis (VL), rectus femoris (RF), and vastus intermedius (VI) muscles are obtained at the midpoint between the anterosuperior iliac spine and the upper edge of the patella, whereas the vastus medialis (VM) is assessed at 30% of the distance between the lateral condyle and the greater trochanter of the femur, based on a previous study [35]. To ensure a similar probe position in subsequent tests, the assessment site of each muscle is marked on transparent paper and used for probe repositioning.

All images will be analyzed using the ImageJ software (National Institutes of Health, USA, version 1.37). The muscle thickness will be assessed as the distance from each muscle’s superior and inferior muscle aponeurosis [45]. Overall quadriceps femoris muscle thickness will be calculated as the sum of each muscle thickness (i.e., RF + VL + VM + VI). Muscle quality will be determined by the echo intensity values, which will be calculated from gray-scale analysis using the standard histogram function in ImageJ (National Institute of Health, USA, version 1.37). A region of interest will be selected in each muscle, including as much of the muscle as possible while avoiding surrounding fascia, and the echo intensity value within the region of interest will be calculated and expressed in values between 0 and 255 (0 = black; 255 = white [46]). The echo intensity of the quadriceps femoris will be calculated as the mean of echo intensity values of the four individual quadriceps femoris muscles ((RF + VL + VM + VI)/4).

##### Functional performance

Functional tests are performed according to the procedures proposed by Rikli and Jones [40].

The Arm Curl test is performed to measure the strength of the upper limbs. Starting at full elbow extension and holding a 2-kg dumbbell in each hand, participants are instructed to perform the maximal number of elbow crunches over the full range of motion for 30 s. The test is performed with both upper limbs.

The 30-s Chair-Stand test is performed to measure the strength of the lower limbs. Participants are instructed to sit and stand up from a chair 43 cm high from the seat, without the aid of the upper limbs, as many times as possible for 30 s.

The 8-ft Up-and-Go test is performed to measure agility and dynamic balance. Participants are instructed to get up from the chair (43 cm), turn around a marker that will be 2.44 m, and return to the starting position. The shortest time of two attempts will be considered as a result.

The Chair Sit-and-Reach test is performed to measure the flexibility of the lower limbs. Participants sit on the front edge of a chair and extend one leg straight out in front of the hip, with the foot flexed and the heel resting on the floor (the other leg is bent, foot flat on the floor). The object is to reach as far forward as possible toward (or past) the toes. The investigator uses a ruler to note the cm left to reach the toe (negative score) or the cm that went past the toe (positive score).

The Back Scratch test is performed to measure the flexibility of the upper limbs. Participants are instructed to try to touch the middle fingers of both hands together behind the back. The investigator uses a ruler noting the cm left to reach the middle fingers (negative score) or the cm that the middle fingers overlapped (positive score).

The 6-min Walk test is performed to measure aerobic fitness. The course proposed in the original test is 45.72 m rectangular. The course will be adapted for a straight line of 30 m in length, demarcated with cones every 3 m. Participants are instructed to walk for 6-min in a flat 30 m course, where the total distance walked “as fast as possible” is assessed.

##### Mental health

HADS was developed by Zigmond and Snaith [47] to evaluate depressive and anxiety symptoms. The instrument was translated and validated for the Brazilian population [48]. HADS consists of 14 items, with seven items forming the anxiety subscale and the other seven forming the depression subscale. It allows for the assessment of symptoms experienced in the previous week. Each item has four response options, ranging from 0 to 3, with each subscale having a maximum score of 21 points.

